### Plans to promote participant retention and complete follow-up {18b}

The centralized follow-up assessment is anticipated to be more challenging than in conventional individual-patient clinical trials because the study uses broad inclusion criteria and the consecutive recruitment of patients; there is a high “floating” population in LMICs where people often change their mobile telephone numbers; and there is a relatively long interval between the time of discharge from hospital and follow-up (6 months). Several strategies are used to ensure that the rate of lost-to-follow-up is kept low. First, investigators emphasize to participating patients (and their responsible person[s]) during the consent process that they are to receive a telephone call from a person in a centralized office to check on their health status at 6 months. Second, the telephone number of the central office is provided on a small card to patients and/or their relatives at the time of discharge from hospital as a reminder to accept the follow-up telephone call. Third, investigators collect a range of contact information, including those of the patient and of several relatives and/or friends. Finally, the investigator will try to reassure patients and relatives of the telephone number to overcome any mistrust of unfamiliar telephone calls.

### Data management {19}

Hospital sites receive paper versions of the CRFs and a procedure manual to serve as a reference guide in using the database; each data element is defined to ensure investigators are accurate and consistent in data entry. All data entry is completed using a password-protected Internet-based data management system which allows individual log-in; all investigators and coordinating/monitoring research staff are required to ensure security, privacy and confidentiality. Only research staff listed on site delegation logs are given access to the data management system, which allows real time data entry and the generation of queries for values entered outside of valid ranges, and for consistency checking. All computerized forms are electronically signed (by use of the unique password) by authorized study staff; all changes made following the initial entry have an electronic dated audit trail.

### Confidentiality {27}

Every precaution is taken to respect the privacy of participants in the conduct of the study. Only de-identified data will be used for statistical analysis and the publication of results to maintain confidentiality. However, as a part of the centralized follow-up service, the International Coordinating Center (ICC) at TGI and Regional Coordinating Centers (RCCs) will use contact sources recorded by the hospital sites. Only name, telephone numbers, next of kin, and primary medical practitioner contact details (if applicable) are sent to the follow-up center for the follow-up assessments. The information is encrypted and password-protected using an MS Excel lock form before being sent by email in batches. This information is included in the PIS and PRIS. In the course of monitoring for data quality and adherence to the study protocol, research staff will refer to source documents (medical records) at participating hospitals. This information is also included in the PIS and PRIS. All individual and site information will be de-identified in reports and results to further protect the confidentiality of participants.

### Plans for collection, laboratory evaluation, and storage of biological specimens for genetic or molecular analysis in this trial/future use {33}

Not applicable. Biological specimens are not collected as part of this study.

## Statistics methods

### Statistical methods for primary and secondary outcomes {20a}

All analyses will be undertaken at the patient level on an intention-to-treat (ITT) basis at each site using generalized estimating equations (GEE) or random-effects regression to account for clustering. The primary outcome of a shift (improvement) in scores on the mRS at 6 months will be analyzed by means of an ordinal logistic regression, with mRS as a dependent variable with 7 levels (0 [no residual symptom] to 6 [death]). The model will include the trial phase (1 to 4), the randomized arm (control or intervention) corresponding to each phase, and the size of the site (as used in the stratification). The secondary outcome of neurological change at 7 days will be analyzed with the same method [28]. Binary and continuous secondary outcomes will be analyzed using a similar approach but using logistic and linear regression, respectively.

All analyses will be adjusted for clustering within center, hospital size (stratification variable), and for trial phase. In addition, sensitivity analyses will be conducted after considering potential prognostic variables as well as the effect of time to adjust for potential background secular trends, including the potential impact of the COVID-19 pandemic.

No adjustment for multiplicity is planned as there are only a small number of pre-specified efficacy outcomes being investigated. A detailed statistical analysis plan will be finalized before unblinding and database locked and posted on a pre-print server.

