### Outcomes {12}

The primary outcome is functional recovery according to the modified Rankin scale (mRS) measured at 6 months and analyzed as an ordinal outcome (shift across all scoring categories of physical function that range from 0 to 5, and death as 6) [22].

Secondary outcomes include death or neurological deterioration according to a change in scores on the National Institute of Health stroke scale (NIHSS) [23] at 7 days, and poor outcome (defined by mRS scores 3–6), separately on death and disability (mRS scores 3–5), HRQoL using the EuroQoL Group 5-Dimension self-report questionnaire (EQ-5D) [24], duration of hospital stay, and residence, all measured at 6 months.

The safety outcomes of any all-cause and cause-specific serious adverse events (SAEs) are recorded according to standard definitions for the duration of follow-up.

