### Methods in analysis to handle protocol non-adherence and any statistical methods to handle missing data {20c}

All analyses including the primary analysis, will be conducted on the ITT population and using all available data. If more than 5% of patients have a missing primary outcome, we will use multiple imputations for sensitivity analysis.

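### Linear regression of hospital stay scores an early in-hospital death as a short, favourable stay, and disability (mRS 3–5) leaves death out of its event, so averted deaths count against the bundle on stay and dilute its effect on disability.

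*Protocol article*

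**What the plan says.** Under *Outcomes {12}* the secondary outcomes include poor outcome (mRS 3–6), then "separately on death and disability (mRS scores 3–5"), then EQ-5D, and "duration of hospital stay, and residence, all measured at 6 months". The primary outcome is the mRS as a "shift across all scoring categories of physical function that range from 0 to 5, and death as 6".

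*Statistical methods {20a}* sets the models for the secondary outcomes: "Binary and continuous secondary outcomes will be analyzed using a similar approach but using logistic and linear regression, respectively". These are patient-level models "using generalized estimating equations (GEE) or random-effects regression to account for clustering", and "All analyses will be adjusted for clustering within center, hospital size (stratification variable), and for trial phase".

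The section on missing data {20c} adds that all analyses "will be conducted on the ITT population and using all available data". Multiple imputation is mentioned only for a missing primary outcome. The article gives no denominator for mRS 3–5, no EQ-5D value for patients who have died, and no rule for a stay that ends in death. Section {20a} announces a detailed SAP, to be finalized before unblinding.

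**The concern.** Death cuts these outcomes short.

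- **Hospital stay.** A patient who dies on day 2 contributes two days to a linear model, which reads as a better result than a survivor discharged on day 15. If the bundle saves that patient, mean stay rises.
- **Disability (mRS 3–5).** A death counts as not disabled if all patients form the denominator, or drops out if only survivors do. Either way, a patient saved into mRS 3–5 adds to the unfavourable count.
- **EQ-5D.** An available-data analysis tends towards survivors only, unless a value is set for death.

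The second research question asks separately about physical function, quality of life and days of hospitalization. No multiplicity adjustment is planned, so each result may be read on its own. At stake is a diluted or misleading answer on these secondary outcomes.

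**Working it through.** **Inputs from the protocol article** (*Sample size {14}*): control mRS 0–6 of 7.6, 18.0, 18.8, 16.6, 19.0, 8.0 and 12.0%; common odds ratio 0.80. So control mRS 3–6 = 55.6%, deaths = 12.0%, and mRS 3–5 = 16.6 + 19.0 + 8.0 = 43.6%.

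**Inputs assumed, not in the documents:** mean stay of 2–7 days for patients who die and 12–20 days for survivors; mean EQ-5D utility of 0.65 in other survivors and 0.0–0.3 in patients saved.

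**Step 1. Reproduce the plan's figure.** Control odds of mRS 3–6 are 0.556/0.444 = 1.252. Multiplied by 0.80 this is 1.002, or 50.0%. The fall is 5.6 points and the relative risk 0.90, as the article states.

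**Step 2. Deaths at the design effect.** Odds 0.12/0.88 = 0.1364; × 0.80 = 0.1091; probability 9.84%. Deaths averted: 12.0 − 9.84 = 2.16 points.

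**Step 3. Hospital stay.** If nobody else's stay changes, the difference in means is (deaths averted) × (survivor stay − stay if dying).

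- Smallest: 0.0216 × (12 − 7) = 0.11 day.
- Largest: 0.0216 × (20 − 2) = 0.39 day.

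The direction holds whenever patients who die have shorter stays than those saved. The calculation treats every averted 6-month death as an in-hospital death; deaths after discharge do not shorten the stay, so on that count it is at the high end. It also gives patients saved the average survivor's stay; a longer one would raise it.

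**Step 4. Disability at the design effect.** Treated mRS 3–5 = 50.05 − 9.84 = 40.2%.

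| Denominator | Control | Treated | Odds ratio |
|---|---|---|---|
| All patients | 43.6% | 40.2% | (0.402/0.598)/(0.436/0.564) = 0.87 |
| Survivors | 43.6/88.0 = 49.5% | 40.2/90.2 = 44.6% | 0.82 |
| mRS 3–6, for comparison | 55.6% | 50.0% | 0.80 |

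On the log scale, ln(0.87)/ln(0.80) = 0.62, so about 38% of the effect is lost with all patients in the denominator. With survivors only, ln(0.82)/ln(0.80) = 0.89, so about 11% is lost.

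**Step 5. Mortality-only scenario.** Move 3 points of deaths (12% to 9%) into mRS 4 and 5, 1.5 points each, and change nothing else. No patient is worse off, and a proportional-odds fit gives a common odds ratio of 0.97. Yet mRS 3–5 rises:

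- All patients: 43.6% to 46.6%; odds ratio (0.466/0.534)/(0.436/0.564) = 1.13.
- Survivors: 49.5% to 46.6/91.0 = 51.2%; odds ratio 1.07.
- mRS 3–6 stays at 55.6%.

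**Step 6. EQ-5D.** With 2.16 points of deaths averted and no other change, the survivors-only difference is (0.88 × 0.65 + 0.0216 × u)/(0.88 + 0.0216) − 0.65, where u is the utility of patients saved. It runs from −0.016 (u = 0) to −0.008 (u = 0.3). With death scored 0 the difference is 0.0216 × u, from 0 to +0.006.

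**The case against.** The strongest reply is that this is SAP detail. The mRS 3–5 denominator and the EQ-5D value at death are commonly left to that plan, which is announced and not shown. For EQ-5D this stands: scoring death 0 is compatible with linear regression, so the article fixes nothing wrong there. For stay it does not, because the article itself names linear regression for an outcome that death ends early. For disability, the definition itself excludes death from the event.

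A second reply is that deaths are counted elsewhere: as mRS 6 in the primary outcome, within mRS 3–6, and as a secondary outcome of their own. A mortality benefit would be visible beside any rise in mRS 3–5. This stands and limits the harm to these secondary outcomes.

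A reader might also draw stronger conclusions that the document does not support:

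- *The bundle would look harmful on disability.* At the protocol's own design effect mRS 3–5 improves under either denominator. Reversal needs an effect made up mainly of deaths averted into disabled survival.
- *Every averted death worsens all three outcomes.* A patient saved into mRS 0–2 leaves mRS 3–5 unchanged among all patients and lowers it among survivors. Survivors-only EQ-5D falls only if patients saved score below the survivor mean.
- *The models ignore the design.* They are GEE or random-effects models adjusted for clustering, phase and hospital size, although this does not cure truncation by death.
- *The distortion is as large as the expected effects on stay or EQ-5D.* The article states no expected effect for either.

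**Conclusion.** The point holds, limited to secondary outcomes. It is firmest for hospital stay, where the stated model gives credit for early death. The distortion there is about 0.1 to 0.4 day at the design effect; its size rests on the assumed stays and on averted deaths being in-hospital deaths, and its direction only on shorter stays in patients who die.

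For mRS 3–5 the expected consequence is dilution, not reversal: an odds ratio of 0.87 in all patients or 0.82 in survivors, against 0.80 for mRS 3–6. These figures rest only on the article's control distribution and proportional odds. The odds ratios of 1.13 and 1.07 belong to a mortality-only scenario that the protocol does not assume.

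For EQ-5D the point is conditional on what the SAP says.

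**What to change.** - **Hospital stay:** replace linear regression with time to discharge alive, treating in-hospital death as a competing event, and keep the adjustment for clustering, phase and hospital size.
- **Disability:** interpret mRS 3–5 only beside death, name its denominator, and make mRS 3–6 the main dichotomy.
- **EQ-5D:** if the SAP does not already do so, analyze utility with death scored 0 and keep survivor-only results as descriptive.

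The cost is minor extra programming and a stay estimate that is less directly interpretable than a difference in days. The stay analysis needs the length of stay, which the outcome already requires, and whether the stay ended in death; the article has deaths recorded to 6 months. Days alive and out of hospital to 6 months would be another option, but the article describes no collection of readmission dates, so its feasibility is not shown. No change to the primary analysis or the sample size is needed.

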**Methods:**

INTERACT3 is a pragmatic, international, multicenter, stepped-wedge (4 phases/3 steps), cluster-randomized controlled trial to determine the effectiveness of a multifaceted care package in adult (age ≥ 18 years) patients (target 8360) with acute ICH (< 6 h of onset) recruited from 110 hospitals (average of 19 consecutive patients per phase) in low- and middle-income countries. After a control phase, each hospital implements the intervention (intensive BP lowering, target systolic < 140 mmHg; glucose control, target 6.1–7.8 mmol/L and 7.8–10.0 mmol/L in those without and with diabetes mellitus, respectively; anti-pyrexia treatment to target body temperature ≤ 37.5 °C; and reversal of anticoagulation, target international normalized ratio < 1.5 within 1 h). Information will be obtained on demographic and baseline clinical characteristics, in-hospital management, and 7-day outcomes. Central trained blinded assessors will conduct telephone interviews to assess physical function and health-related quality of life at 6 months. The primary outcome is the modified Rankin scale (mRS) at 6 months analyzed using ordinal logistic regression. The sample size of 8360 subjects provides 90% power (*α* = 0.05) to detect a 5.6% absolute improvement (shift) in the primary outcome of the intervention versus control standard care, with various assumptions.

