Clustering interventions together as part of a care bundle have shown encouraging results. For example, the Australian Quality in Acute Stroke Care (QASC) cluster trial [19] showed that a protocol to manage fever, hyperglycemia, and assessments of swallowing function improved recovery for patients with acute stroke, while a quality improvement “before-and-after” evaluation of protocol involving anticoagulation reversal, intensive BP lowering, and rapid triage and access to neurosurgery and critical care showed improved survival in patients with ICH admitted to hospitals in Greater Manchester, UK [20]. Our analyses of the second phase of INTEnsive blood pressure Reduction in Acute Cerebral hemorrhage Trial (INTERACT2) showed that the scoring of abnormal baseline variables covering BP, glucose, body temperature, and prior use of anticoagulants independently predicted poor outcome in ICH [21].

We therefore initiated the third INTEnsive care bundle with blood pressure Reduction in Acute Cerebral hemorrhage Trial (INTERACT3) with collaborators in 10 Asian, Latin American, and African countries (Appendix 1) to determine the effectiveness of a goal-directed care bundle of active management involving early physiological control (intensive BP lowering, glycemic control, and pyrexia treatment) and reversal of anticoagulation, compared against usual standard of care. Using a pragmatic, one direction, stepped-wedge, cluster-randomized controlled trial design, the aims are to provide evidence of the applicability of a readily scalable, goal-directed protocol that could be widely applied in clinical practice, while also providing information on the effectiveness of particular components and across certain characteristics of patients. Herein, we report the final version of the trial protocol, compliant with the Standard Protocol Items: Recommendations for Interventional Trials (SPIRIT) reporting guideline (Appendix 2).

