We recognize there will be variability in the number of patients who will be recruited at each site, with very large hospitals recruiting as many as 50 patients per phase while smaller hospitals may only recruit a few patients per phase. If the sample size was inflated to accommodate this issue as has been used in parallel cluster trials [26] (e.g., using an inflation factor of approximately 1.3), the sample size would need to reflect 25 patients per site per phase (i.e., 11,000 patients in total). However, given that this adjustment would be a very conservative scenario and that the effect of variability in cluster sizes is expected to be mostly mitigated by the randomization process, including stratification by size [27], we have elected to maintain the target average of 19 patients per site per phase for a total sample size of 8360 patients. Assuming a worst-case scenario for the effect of cluster size variability on power, this sample size would still provide at least 80% power to determine the proposed treatment effect.

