## Assignment of interventions: blinding

### Who will be blinded {17a}

The treatment is open label to both investigators and patients at sites. All other investigators, statisticians, and endpoint assessors are blind to the treatment allocation, who are trained to collect outcome measures by telephone at 6 months.

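### The primary mRS model leaves out baseline severity; prespecifying it would cheaply gain power and guard against intervention-related differences in who is enrolled

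*Protocol article*

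**What the plan says.** Protocol article, section Statistical methods for primary and secondary outcomes {20a}, on the primary ordinal logistic regression: "The model will include the trial phase (1 to 4), the randomized arm (control or intervention) corresponding to each phase, and the size of the" recruiting hospital. The same section adds: "All analyses will be adjusted for clustering within center, hospital size (stratification variable), and for trial phase". No patient-level baseline variable is in the primary model. Prognostic factors come in afterwards: "sensitivity analyses will be conducted after considering potential prognostic variables", together with further work on secular trends and COVID-19. The section also promises a detailed SAP, final before unblinding and posted publicly.

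The data for adjustment are planned. The abstract says: "Information will be obtained on demographic and baseline clinical characteristics, in-hospital management, and 7-day outcomes". Table 1 marks GCS, NIHSS, medical history and brain imaging at baseline. The Background and rationale {6a} reports from the group's previous trial that "the scoring of abnormal baseline variables covering BP, glucose, body temperature, and prior use of anticoagulants independently predicted poor outcome in ICH".

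On enrolment, section Who will be blinded {17a} states: "The treatment is open label to both investigators and patients at sites". A participant is defined by individual consent to data collection (Hospital sites), and eligibility rests on the attending clinician's reading of the criteria (Study patient characteristics).

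**The concern.** Two things are at stake.

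**Precision.** Severity at presentation should be strongly prognostic, and the Discussion stresses a broad case mix, including large hematomas and patients needing early surgery. A primary model that ignores severity leaves avoidable noise in the estimate. This bears on the sample-size decision: in Sample size {14} the sponsor considered inflating to 11,000 patients for unequal site sizes, then wrote "we have elected to maintain the target average of 19 patients per site per phase" and accepted at least 80% power in the worst case.

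**Comparability.** Randomizing sites to a switching time does not randomize patients. Staff know whether their site has switched, consent is sought patient by patient, and one exclusion is a judgement about likely adherence. If the patients enrolled under the bundle are slightly milder or more severe than those enrolled under usual care at the same site, a model with only phase, arm and site size attributes the difference to the bundle. The protection against this is placed in a secondary analysis, so if the two results disagree, the less protected one leads.

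**Working it through.** **1. Inputs (Sample size {14}).** Common odds ratio 0.80; α 0.05 (two-sided assumed); power 90%; control mRS 7.6/18.0/18.8/16.6/19.0/8.0/12.0%; ICC 0.044; 110 sites, 3 groups, 4 phases; 18 evaluable patients per site-phase (19 after 5% missing); inflation factor 1.3 for unequal site sizes. R² is not given, so I assume 0.1 to 0.4.

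**2. Reproducing the plan's size.** Averaging the control distribution with the one implied by an odds ratio of 0.80 gives Σp̄³ = 0.0272.

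- Individually randomized total (Whitehead): 12(1.960 + 1.282)² / [(ln 0.80)²(1 − Σp̄³)] = 12 × 10.507 / (0.04979 × 0.9728) = 2603.
- Stepped-wedge design effect (Woertman; 3 steps, 18 per site-phase): [1 + 0.044 × 71] / [1 + 0.044 × 44] × 3(0.956) / [2(3 − 1/3)] = 4.124 / 2.936 × 0.5378 = 0.755.
- Sites: 2603 × 0.755 / 18 = 109.2, against 110 planned.

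**3. Reproducing the power (Hussey–Hughes).** Per-patient variance on the log-odds scale is 3/(1 − Σp̄³) = 3.084. Then τ² = 0.044 × 3.084 = 0.1357 and σ² = 0.956 × 3.084 / 18 = 0.1638. With 37/37/36 sites per group: I = 110, T = 4, U = 221, W = 18,945, V = 517.

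Var = Iσ²(σ² + Tτ²) / [(IU − W)σ² + (U² + ITU − TW − IV)τ²] = 110 × 0.1638 × 0.7065 / [5365 × 0.1638 + 13,431 × 0.1357] = 0.00471.

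The SE is 0.0686, so power = Φ(0.2231/0.0686 − 1.96) = 90.2%. With 18/1.3 = 13.8 per site-phase it is 82.3%. Both stated figures (90% and at least 80%) hold without any covariate.

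**4. Adding severity.** Multiply the within-site variance by (1 − R²) and leave τ² unchanged:

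| Assumed R² | SE ratio (18 per site-phase) | Power, 18 per site-phase | Power, 13.8 per site-phase |
|---|---|---|---|
| 0 | 1.000 | 90.2% | 82.3% |
| 0.1 | 0.953 | 92.6% | 85.7% |
| 0.2 | 0.903 | 94.9% | 89.1% |
| 0.3 | 0.850 | 96.9% | 92.4% |
| 0.4 | 0.791 | 98.4% | 95.4% |

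This is a linear-model approximation. In proportional-odds regression, adjustment does not generally shrink the SE of the log odds ratio. Power rises because the conditional odds ratio lies further from 1. The table therefore indicates the likely size of the gain; it is not an exact result for the planned model.

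**5. Case mix.** The simulation had 110 sites, 4 phases, 18 patients per site-phase and no treatment effect. The mRS was scored and analyzed linearly with site and phase effects, in 500 runs per scenario. Each cell shows latent R² 0.23 / 0.41.

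| Shift in mean severity | Rejection, no severity term | Rejection, severity adjusted |
|---|---|---|
| 0.1 SD per phase, all sites | 5.6% / 2.8% | 3.8% / 4.0% |
| 0.2 SD per phase, all sites | 6.4% / 6.6% | 6.2% / 6.2% |
| 0.05 SD under intervention | 6.4% / 10.0% | 4.2% / 4.0% |
| 0.1 SD under intervention | 23.4% / 34.2% | 4.4% / 5.0% |
| 0.2 SD under intervention | 61.2% / 83.0% | 4.4% / 3.8% |

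Monte Carlo error at a true 5% is √(0.05 × 0.95/500), about 1 point. Across all runs (300–500 per scenario) the unadjusted rejection rates were 6–15%, 19–34% and 59–85% for the three intervention-related shifts, and about 4–8% after adjustment. The adjusted column assumes that the covariate captures the whole shift. NIHSS or GCS would capture only the part they measure.

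**The case against.** The strongest reply is that nothing here is wrong. A primary model without patient-level covariates, followed by an adjusted sensitivity analysis, is a legitimate choice, and the trial is sized to reach its power that way. That stands.

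The article also contains safeguards. Eligible patients are enrolled consecutively (Recruitment {15}). Every acute ICH patient is registered, including those screened but not included, so selection can be examined (Hospital sites). Sites receive the intervention protocol only after the control phase (Strategies to improve adherence {11c}). These reduce the risk of arm-related enrolment but do not remove it, given open-label sites, individual consent and clinician-judged eligibility.

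Several stronger readings are tempting, and the article does not support them:

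- A reader might infer that case-mix drift between phases contaminates the headline result. Phase is in the primary model, and the simulation shows that common drift is absorbed.
- A reader might infer that the trial is underpowered, or that a sample-size equivalent of the gain can be quoted. The stated power reproduces, R² is assumed, and the variance formula does not carry over directly to a log odds ratio.
- A reader might take the sensitivity-analysis wording as permission to choose covariates after seeing results. The promised SAP, final before unblinding, answers that, and naming the covariates can properly be left to it.
- A reader might take Table 1 to mean that NIHSS and GCS exist for every patient. It schedules them and says nothing about completeness.
- A reader might suppose that inflation to 11,000 was refused on cost. The reason given is statistical: the adjustment was judged very conservative and largely mitigated by stratified randomization.

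**Conclusion.** The point holds as a worthwhile, inexpensive improvement to a valid plan. The primary model forgoes baseline severity data that the trial already schedules.

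For an assumed R² of 0.1 to 0.4, the forgone power is roughly 2 to 8 percentage points on the nominal design and 3 to 13 points in the cluster-size worst case, on a linear approximation. The gain matters most in the worst case, where the margin over 80% is thin.

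The second benefit concerns validity. A severity shift of 0.1 SD tied to the intervention would raise the false-positive rate of the unadjusted analysis to about 19–34%, and adjustment for the measured part of that shift would largely correct it. The article gives no evidence that such a shift has occurred or how large it might be. It shows only that the design permits one.

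**What to change.** In the SAP, before unblinding, add a short fixed list to the primary ordinal model: age, sex, baseline NIHSS or GCS (choose one), and time from onset to presentation. State how each is entered. Use simple imputation for missing baseline values so that no patient drops out of the analysis. Report the model with phase, arm, site size and clustering alone as the sensitivity analysis, and say in advance that the adjusted result leads if the two differ. Hematoma volume is best left out of this list unless it is recorded for all patients, since central image analysis is described only for the 1000-patient subset.

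The cost is analysis-plan wording, with no new data and no change to trial conduct. The one real downside is that the odds ratio becomes conditional on baseline severity and is no longer directly the 0.80 used for sizing. State this in the SAP and the report, and show the unadjusted odds ratio beside the adjusted one.
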